The current pilot study is designed as a first test of the newly developed protocol of structured EFFT. Therefore, it is important to evaluate whether such treatment is desirable and feasible, and establish an initial indication of its effectiveness. Evaluation of the feasibility of EFFT will be based on semi-structured interviews with family members who participated in order to obtain their evaluation of (specific phases of) EFFT and to identify possible points of improvement of EFFT. Concerning the effectiveness of EFFT, only one early pilot study is available that has shown EFFT to be a promising intervention for families with children suffering from bulimia [19]. However, we expect EFFT to be effective since emotionally focused couples therapy (EFCT), of which EFFT is a fundamental extension, is an empirically supported treatment [20]. In this study we will examine the effectiveness of structured EFFT with regard to several outcomes. We chose escalation in negative interactions between child, mother and father as the primary outcome measure as the transdiagnostic idea that the child’s problems are originating in and/or exacerbated by negative interactions within the family is central to EFFT. Other equally important outcome measures are accessibility and responsiveness of the parents to the child’s and their partner’s needs, attachment between the parents and the child, and child psychological complaints. Additional outcome measures are: disciplining of the child by the parents; attachment between the parents as partners, and parental relationship satisfaction. Concerning all outcomes, we hypothesize:

less change during the waiting period compared with the treatment phase;gain during the treatment phase; andsubstantial maintenance during follow-up.

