## Method

### Design

A within-subjects design with three waves will be used. The waiting period will span approximately two months, the treatment phase will last three to four months, followed by a two months follow-up period concluded with a booster session. A randomized controlled design was deemed not feasible for this pilot study, we therefore opted for a within-subjects design in which families will serve as their own controls. By comparing change during the waiting period with change during the treatment phase, we probably get an impression of spontaneous remission vs. treatment-related change.

The study will use a multi-method approach. Evaluation of the effectiveness of EFFT will be based on self-report questionnaires, whereas evaluation of feasibility will be based on semi-structured interviews, self-reported ratings by the family members and the registered treatment attendance rates. Finally, adherence to the treatment protocol by the therapists is based on the roadmap for structured EFFT (S1 File).

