### Statistical analyses

As scores are not independent *within* respondents (repeated measurements) and *between* respondents (three dyads: mother and the adolescent, father and the adolescent, and the parents as partners) multi-level analyses are preferred. However, concerning multilevel models with three levels no agreed upon power analyses are available. Therefore, we estimated study power based on a repeated measurements ANOVA with GPower 3.1.9.7 [30]. We anticipate an effect size of *d* = 0.7 which is based on effect sizes obtained by Attachment-Based Family Therapy, which is akin to EFFT (i.e., *d* = .97 [31] and *d* = 1.08 [32]), and the average effect size we obtained with a Couple relationship Education course based on EFT (i.e., *d* = 0.6 [24]). We computed the required sample size to detect this effect size of *d* = 0.7 with a power of .8 an alpha of .05 and a correction for sphericity of e = .5. It was calculated we would need *n* = 20 families. This is a conservative power-estimation based on the number of families as if we only had one person in each family reporting on the outcome measures. However, as several of our outcomes are dyadic by nature (e.g., outcomes regarding interaction patterns between mother and the adolescent, father and the adolescent, and father and mother as partners) the actual power will be higher as the number of individuals will be twice as high for these outcomes.

Following the power analysis we first plan to run a repeated measurements ANOVA to test our main hypothesis concerning change during treatment plus follow-up on the primary outcome. Subsequently, Linear Mixed Models (LMM) in SPSS will be applied with repeated measurements (level 1) nested within respondents (level 2) and, depending on the specific outcome, respondents nested within the dyad of interest (level 3) [33]. In this way we will be able to assess change over time. An advantage of LMM is the possibility to use cases with partial missing data. To adjust for interdependence of the repeated measurements, the AR1 covariance structure will be applied, and to adjust for interdependence of respondents, we will include an intercept at level 3. When results of the multilevel model converge with the repeated measures ANOVA, trust in the robustness of findings will be enhanced.

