We will examine change during the waiting period (comparison of pre-treatment versus pre-waiting period assessments), change during treatment (post-treatment versus pre-treatment assessments), change during follow-up (booster session versus post-treatment assessments), and change during the whole study period (follow-up versus pre-waiting period assessments). We will compute effect sizes (Cohen’s *d*s) using, per comparison, the estimated marginal means, and the pooled standard deviations of the corresponding raw means [34]. Effect sizes will be interpreted as small when Cohen’s *d* is 0.35 or below, moderate when 0.36−0.65, and large when 0.66 or higher. [35]. To evaluate missingness at random, we will apply pattern-mixture models for the dependent variables [36].

The feasibility of EFFT will be evaluated with multiple methods. First, the widely used MAXQDA software will be applied for the qualitative analyses of the semi-structured interviews. We will follow the steps described by Boeije [37]. for inductive thematic analysis. This starts with open coding: fragments relevant to answering the main question will be labeled. Then, several rounds of axial coding will take place where emerging themes within and between participants will be labeled. Finally, the emergent themes will be integrated into an exhaustive representation that describes the overall experience of the families. Second, treatment attendance based upon registrations will be calculated. Finally, treatment adherence will be evaluated by calculating the extent to which the treatment protocol has been executed by the therapists based on ratings by independent raters.

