## Discussion

Ample support has been found for the notion that adolescent’s mental health problems are rooted in, and exacerbated by, insecure attachment relations characterized by dysfunctional emotional regulation within families. EFFT aims at developing secure attachment and functional emotional regulation. The current pilot study will be the first to examine feasibility and the potential effectiveness of EFFT. We adapted the original EFFT as described by Furrow et al. [5] and developed structured EFFT to reduce complexity inherent to family interventions.

Notable strengths of this study are the repeated measurements and the inclusion of a waiting period and a follow-up. The waiting period is important in examining spontaneous remission (reduction of complaints and insecure attachment without treatment), whereas the follow-up is important to get an impression of post-treatment maintenance of treatment gain. Repeated measurements are important to get more detailed insight into change over time and to enhance statistical power.

An important limitation of the study is the fact that its design is uncontrolled. This means that change during treatment cannot be attributed with 100% certainty to the intervention as spontaneous remission remains a possible explanation. To account for this, we included a waiting period. When change during treatment is larger than change during the waiting period it is likely it can be attributed to EFFT. Other limitations are the limited size of the convenience sample recruited by private practices, meaning that generalizability over various disorders should be interpreted with caution. Therefore, we plan a larger controlled study in the future to assess the effectiveness of EFFT as a transdiagnostic intervention for families.

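### The plan's first hypothesis, that families change less while waiting than during treatment, has no specified test or interval, and the stated power does not apply to it

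*Protocol article*

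**What the plan says.** The Introduction gives three hypotheses for all outcomes. The first is "less change during the waiting period compared with the treatment phase". The Design section makes this the purpose of the waiting period: "By comparing change during the waiting period with change during the treatment phase, we probably get an impression of spontaneous remission". The Discussion turns it into a rule for attribution: "When change during treatment is larger than change during the waiting period it is likely it can be attributed to EFFT".

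The Statistical analyses section then sets out:

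- A main test: "we first plan to run a repeated measurements ANOVA to test our main hypothesis concerning change during treatment plus follow-up on the primary outcome".
- A linear mixed model with repeated measurements at level 1, described in general terms as a way to assess change over time.
- Four comparisons, each with its own Cohen's d. The first is "change during the waiting period (comparison of pre-treatment versus pre-waiting period assessments") and the second is "change during treatment (post-treatment versus pre-treatment assessments"). The other two are booster session against post-treatment, and follow-up against pre-waiting.
- A power calculation for a repeated-measures ANOVA with d = 0.7, power 0.8, alpha 0.05 and a sphericity correction of 0.5, which gives 20 families. The Participants section aims for 15 to 20.

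**The concern.** The waiting period is the only control in this trial. The quantity that uses it is the change during treatment minus the change during waiting. The main ANOVA, read naturally, runs from pre-treatment onward (t2 to t5) and so does not involve the pre-waiting assessment. The four comparisons supply the two components (t2 against t1, t4 against t2) but not their difference.

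With nothing more specified, the first hypothesis is left to an informal reading of two separate results. A significant main result would be a pre–post finding without control. The conclusion the article wants, change beyond spontaneous remission, would come with no standard error, no interval and no stated precision. The article itself sets out the hypotheses, the main test, the list of comparisons, the effect-size method and the power basis. The gap is therefore a mismatch between its own parts, not only detail left to a fuller document.

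**Working it through.** **1. Hypothesis against analysis.** With t1 = pre-waiting, t2 = pre-treatment, t4 = post-treatment and t5 = pre-booster:

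| Element | Quantity |
|---|---|
| Hypothesis 1 | (t4 − t2) against (t2 − t1) |
| Main ANOVA | time effect over treatment and follow-up |
| Comparison 1 | t2 − t1 |
| Comparison 2 | t4 − t2 |
| Comparison 3 | t5 − t4 |
| Comparison 4 | t5 − t1 |

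No row below the first is a difference between two changes.

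**2. The plan's own figure.** For a one-group repeated-measures ANOVA with m occasions, f = d/2 = 0.35 and ε = 0.5:

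λ = f²·n·m·ε/(1 − r), df1 = (m − 1)ε, df2 = (n − 1)(m − 1)ε.

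The article states neither m nor r. With m = 4 and r = 0.5 (assumed), n = 20 gives λ = 0.1225 × 20 × 4 × 0.5/0.5 = 9.8 and power 0.805, so the stated 20 is reproduced. Other pairs also give 20: m = 5 with r of about 0.42 to 0.44, and m = 3 with r of about 0.58 to 0.60. At r = 0.5, m = 5 gives 18. In every case the calculation concerns an overall time effect.

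**3. Power for the own-control contrast.** The contrast is C = (t4 − t2) − (t2 − t1) = t4 − 2·t2 + t1. Assumptions not in the article: equal SDs, compound symmetry with correlation r, no true change while waiting, one report per family, two-sided alpha 0.05.

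Var(C) = (1 + 4 + 1) − 4r − 4r + 2r = 6(1 − r), in SD² units.

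At r = 0.5, SD(C) = √3 = 1.73 and dz = 0.7/1.73 = 0.404. For comparison, SD(t4 − t2) = √(2(1 − r)) = 1.00, so dz = 0.70 and power is 0.84 at n = 20. Noncentral-t results for C:

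| r | dz | Power, n = 15 | Power, n = 20 | n for 0.8 |
|---|---|---|---|---|
| 0.3 | 0.342 | 0.23 | 0.31 | 70 |
| 0.5 | 0.404 | 0.31 | 0.40 | 51 |
| 0.7 | 0.522 | 0.47 | 0.60 | 31 |
| 0.8 | 0.639 | 0.63 | 0.77 | 22 |

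An AR(1) structure by occasion gives 0.29 to 0.75 at n = 20 over the same correlations. If waiting brings a change of d = 0.2, power at r = 0.5 and n = 20 falls to 0.23. A one-sided test at r = 0.5 and n = 20 gives 0.54.

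**4. Expected precision.** At n = 20 and r = 0.5 the 95% interval for C has a half-width of about 2.093 × 1.73/√20 = 0.81 SD, against an anticipated difference of 0.7 SD.

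**5. What an informal reading does.** Simulation with 20 families, the same true change in both phases (d = 0.4 each) and r = 0.5:

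- The treatment point estimate exceeds the waiting estimate in about 50% of trials.
- Treatment is significant and waiting is not in about 30%.
- A direct two-sided test of C wrongly favours treatment in about 2.5%.

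**The case against.** This is a feasibility pilot. The article speaks only of an impression of spontaneous remission, names the uncontrolled design as an important limitation and plans a larger controlled study. Low power for such a contrast is to be expected with 15 to 20 families. The mixed model could yield the contrast, and the Design section does state the comparison in words: "By comparing change during the waiting period with change during the treatment phase". All of this stands. It argues for estimation with an interval rather than a powered test, but not for leaving the contrast out of a list that names every other comparison.

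Four stronger readings are tempting and are not supported:

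- **That 20 families shows the pre-waiting assessment was left out of the power calculation.** It does not. Three, four or five occasions all give 20 at plausible correlations, and neither input is stated.
- **That the article claims 0.8 power for the first hypothesis.** It does not. It ties the power analysis to the ANOVA on treatment plus follow-up. It only fails to say that the first hypothesis lies outside it.
- **That the plan will judge the first hypothesis by one phase being significant and the other not.** No section says so. The Discussion speaks of the larger change, with no procedure attached.
- **That gain during treatment is left to a test without direction.** The comparison of t4 with t2 is already planned, with its own effect size.

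The power figures also depend on assumptions. Dyadic reports, which the article says double the number of individuals for some outcomes, would raise power by an amount that cannot be computed without a within-family correlation. A one-sided test of this directional hypothesis would raise it too.

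**Conclusion.** The concern holds in this form: the first hypothesis, on which attribution to EFFT rests, has no specified test or interval, and the power calculation does not cover it. Under the working's assumptions, power for the own-control contrast is about 0.40 with 20 families and 0.31 with 15 at correlation 0.5. It stays below 0.8 two-sided at 20 families for every correlation from 0.3 to 0.8. These are illustrations, because the article gives no correlation and no anticipated waiting change. The mismatch between hypothesis and analysis does not depend on them.

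This should be fixed, but it does not invalidate the study. The data needed are already collected at all five occasions, the model is already planned, and the article is open about its lack of a control group.

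**What to change.** In Statistical analyses:

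1. Name (t4 − t2) − (t2 − t1), estimated from the five-occasion mixed model, as the analysis of the first hypothesis. Report it as an estimate with a 95% confidence interval.
2. Because waiting lasts about two months and treatment three to four, steady spontaneous improvement alone would make the treatment change larger. Report the contrast per unit time as well, as a sensitivity analysis.
3. State that the 0.8 power applies to the within-subject time effect only, and that the own-control contrast is estimated, not powered.
4. Tie the attribution sentence in the Discussion to this estimate and its interval, not to which of two changes is larger.

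The cost is a paragraph of wording and one extra contrast, with its per-unit-time version, from a model already planned. No further families or assessments are needed. The drawback is a less favourable statement of power for the first hypothesis.

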### Data management

The data will be saved under administration numbers to which each family member is linked and stored on the protected ICT environment of the University of Amsterdam. The data analysis will be performed at the University of Amsterdam. Personal data will be handled conform the General Data Protection Regulation.

## Discussion

Ample support has been found for the notion that adolescent’s mental health problems are rooted in, and exacerbated by, insecure attachment relations characterized by dysfunctional emotional regulation within families. EFFT aims at developing secure attachment and functional emotional regulation. The current pilot study will be the first to examine feasibility and the potential effectiveness of EFFT. We adapted the original EFFT as described by Furrow et al. [5] and developed structured EFFT to reduce complexity inherent to family interventions.

Notable strengths of this study are the repeated measurements and the inclusion of a waiting period and a follow-up. The waiting period is important in examining spontaneous remission (reduction of complaints and insecure attachment without treatment), whereas the follow-up is important to get an impression of post-treatment maintenance of treatment gain. Repeated measurements are important to get more detailed insight into change over time and to enhance statistical power.

An important limitation of the study is the fact that its design is uncontrolled. This means that change during treatment cannot be attributed with 100% certainty to the intervention as spontaneous remission remains a possible explanation. To account for this, we included a waiting period. When change during treatment is larger than change during the waiting period it is likely it can be attributed to EFFT. Other limitations are the limited size of the convenience sample recruited by private practices, meaning that generalizability over various disorders should be interpreted with caution. Therefore, we plan a larger controlled study in the future to assess the effectiveness of EFFT as a transdiagnostic intervention for families.

## Abbreviations

ARE: Accessibility, Responsiveness, Emotional Engagement questionnaire
CSI-4: Couple Satisfaction Index
ECR-RS: Experiences in Close Relationships—Relationship Structures questionnaire
EFFT: Emotionally Focused Family Therapy
RDS: Relationship Dynamics Scale
SEPTI-TS: Self-Efficacy for Parenting Tasks Index Toddler Scale
SDQ: Strengths and Difficulties Questionnaire
